### Study settings and population

Rural Bangladesh is almost demographically and geographically homogeneous. Therefore, the selected sub-districts will be representative of two union parishads (5 villages) for the intervention group and two union parishads (5 villages) for the control group of the rural community of Bangladesh. Parents with children aged 1–4 years in these two groups will comprise the study population.

### Sample size calculation

The following formulae for hypothesis testing of the two group comparison was used [16] *N* = {Z1 – α/2 √2P̃ (1 – P̃) + Z1 – β √P1 (1 – P1) + P2 (1 – P2)}^2^ / (P1 – P2)^2^. P1 = Proportion of drowning in boy children aged under five years 55 % = 0.55; and P2 = Proportion of drowning in girl children aged under five years 45 % = 0.45 [17]. P̃ = (P1 + P2)/2 = 0.5 and adjusting for 10 % non-response *N* = 392+ 10 % of 392 = 431. A sample size of *N* = 431 in each study group would have 80 % power for a Chi-Square Test (*α* = 5 %, 2 *sided*) in order to detect this difference based on a calculation using G-Power. As union participants are nested within villages, a potential design effect needs to be considered. An assumed number of participants per village of 30 and an intra-cluster correlation coefficient of 0.05 could be expected. This would result in a design effect = 1+ (m-1) × ICC = 1+ (20–1) × 0.05 = 1.95. Multiplying this design effect by the “required size for an unnested sample (*N* = 431)” results in a required sample size of *N* = 840 per study group and a total of *N* = 1680 study participants.

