**Method/design:**

A two-arm cluster randomized community trial will be conducted to test the efficacy of the mobile coach intervention for childhood drowning on parents with children below five years of age and compared to an assessment only control group. A total of 1680 parents in the villages with children aged below five years of age will participate. The village will be used as a randomized unit, randomly assigned to an intervention group (*N* = 840) receiving the mobile coach based intervention or an assessment only control group (*N* = 840). An individualized mobile coach intervention based on the demographic data and the individual will be developed, and SMSs, audio messages, videos and images about childhood drowning will be sent to the participants of the intervention group over a period of six months. The participants will receive per week one text message (SMS) and image and one video and audio text per month. The primary outcome measure will be increased knowledge and safety awareness, and behaviour practice about childhood drowning assessed at the six-month follow-up, and the secondary outcome measure will be the reduced incidence of childhood drowning in Bangladesh. The study assistants conducting the baseline and the follow-up assessments will be blinded regarding the group assignment.

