### Outcomes

The outcomes of the study will be to determine the knowledge, awareness and behaviour practices about childhood drowning, as well as the risk factors, and reduce the incidence of childhood drowning. To determine the knowledge pertaining to childhood drowning, five questions about the knowledge of childhood drowning are provided. The questions will be answered YES or NO. A correct answer will score one mark and a zero mark will be given for an incorrect answer. The participants will be classified as having knowledge of drowning if they correctly answer all five questions. Based on those five questions, the total summated score will be calculated. Five questions will be used to measure the awareness about childhood drowning. Based on the five questions, the total summated score will be calculated. The behaviour practices will be divided into supervision practices and swimming ability. In addition, five questions will be used to measure the behaviour practices. Based on the five questions, the total score will be calculated. The study assistants will conduct the six-month follow up assessment by field interviews. The primary outcome will be the monthly assessment of increased knowledge, and safety awareness and practice about childhood drowning. The secondary outcome will be the assessment of reducing the incidence of children drowning to compare the baseline data and end line data, and also to determine the risk factors for childhood drowning. Finally, the outcome variables will be the effects of the mobile coach Intervention on the community in Bangladesh.

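### The sample size is powered for boys' versus girls' shares of drowning, so the stated 80% power does not apply to intervention versus control on the primary outcome

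*Protocol article*

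**What the plan says.** In the protocol article, Sample size calculation, the first input, P1 = 0.55, is described as the "Proportion of drowning in boy children aged under five years". The second input, P2 = 0.45, is the corresponding figure for girls. Both go into a two-proportion formula. After an allowance for non-response, the section says that 431 "in each study group would have 80 % power for a Chi-Square Test" at a two-sided 5% level, and ties that power to the boy–girl contrast with the words "in order to detect this difference based on a calculation using G-Power". A design effect of 1.95 then takes 431 to 840 per group and 1680 in total.

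The primary outcome is elsewhere. The abstract states: "The primary outcome measure will be increased knowledge and safety awareness, and behaviour practice about childhood drowning assessed at the six-month follow-up". Design and main hypothesis makes the comparison intervention versus assessment-only control. Drowning incidence is a secondary outcome there, in the abstract and under Outcomes. For the knowledge items, Outcomes says: "Based on those five questions, the total summated score will be calculated". Awareness and practice are likewise totals over five questions. Outcomes also classes a parent as having knowledge if all five answers are correct.

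**The concern.** The only difference defined in the calculation is boys against girls. Children's sex is not randomised, and the contrast says nothing about the mobile coach. The two figures also sum to 1, so they read as the two sexes' shares of one set of drownings. They do not read as outcome proportions in two independent groups, which is what the formula assumes.

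The calculation contains no control-arm level, standard deviation or target effect for knowledge, awareness or practice. The test it names, a chi-square test of proportions, is also not the one Data analyses gives for the primary scores, which is a t-test (paired, before against after).

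At stake is the only justification for N. If the 80% belongs to another contrast, 840 per arm has no stated rationale for the primary outcome, and a null result cannot be set against any effect the trial was designed to detect.

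**Working it through.** **1. The plan's own figure.** Inputs from Sample size calculation: P1 = 0.55, P2 = 0.45, mean 0.50, two-sided 5%, 80% power.

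n = {1.960 × √(2 × 0.5 × 0.5) + 0.8416 × √(0.55 × 0.45 + 0.45 × 0.55)}² / 0.10²
= (1.3859 + 0.5921)² / 0.01 = 3.9126 / 0.01 = 391.3, rounded up to 392.

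392 × 1.10 = 431.2, taken as 431. 431 × 1.95 = 840.45, taken as 840. The printed figures reproduce. The power at 392 per group is 80.1%, for 0.55 against 0.45.

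**2. Could 0.55 and 0.45 be arm-level drowning risks?** No. Background gives 156.4 drownings per 100,000 rural children aged 1–4. Taking that as an annual rate, and assuming one child per participant, the expected count per arm over six months is 840 × 0.001564 × 0.5 = 0.66. With the risk halved, power would be about 5%, even with no design effect.

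**3. What 840 per arm can detect on the primary outcome.** The protocol gives no SD, so the result is in SD units. Assumptions: 10% loss, leaving 840 × 0.9 = 756 per arm; ICC 0.05; equal village sizes; k villages per arm; no gain from baseline adjustment.

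- Analysed parents per village: m = 756 / k
- Design effect: DE = 1 + (m − 1) × 0.05
- Effective size per arm: n_eff = 756 / DE
- Detectable difference: d = (t₀.₉₇₅ + t₀.₈₀) × √(2 / n_eff), with 2k − 2 degrees of freedom

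| Villages per arm | Source | m | DE | n_eff | df | t₀.₉₇₅ + t₀.₈₀ | d (SD) |
|---|---|---|---|---|---|---|---|
| 42 | 840 / 20, cluster size used in the design effect | 18 | 1.85 | 408.6 | 82 | 1.989 + 0.846 | 0.20 |
| 28 | 840 / 30, cluster size stated in the text | 27 | 2.30 | 328.7 | 54 | 2.005 + 0.848 | 0.22 |
| 15 | Baseline survey | 50.4 | 3.47 | 217.9 | 28 | 2.048 + 0.855 | 0.28 |
| 5 | Study settings and population | 151.2 | 8.51 | 88.8 | 8 | 2.306 + 0.889 | 0.48 |

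On the same basis, power for a 0.20 SD difference is about 81% with 42 villages per arm, 52% with 15 and 22% with 5.

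**4. A binary version.** If the outcome were the proportion with all five answers correct, and the effective size were the plan's 392 per arm, power for a 10-point gain would be 80% to 99.7% over control proportions from 5% to 80%. For a 5-point gain it would be 29% to 76%. These control proportions are assumptions; the protocol gives none.

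**The case against.** The strongest reply is that the inputs are badly labelled but harmless. A 10-point difference centred on 50% has the largest binomial variance, so the same N gives at least 80% power for a 10-point between-arm gain at almost any control level. Its standardised size, 2·arcsin√0.55 − 2·arcsin√0.45 = 0.2003, nearly equals the 0.20 SD in the first row of the table. Replacing the boy and girl figures therefore need not change N. The rise to 0.28 and 0.48 SD comes from the conflicting village counts, which is a separate fault. All of this stands, and it limits the claim: the trial has not been shown to be underpowered by this error. It does not rescue the power statement, because the protocol nowhere offers 10 points as a target effect of the intervention.

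A second reply is that the mismatch of tests is weaker than it looks. Knowledge can be scored as all five correct, Data analyses also reports proportions, and the only t-test named is a paired one. One mark per correct answer is stated for knowledge only, so a 0–5 range for the other two domains is an inference. That is fair: a two-proportion calculation would suit the binary knowledge outcome. But 0.55 and 0.45 are not expected proportions of parents with knowledge.

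A third reply is that differences by children's gender are the first of the Specific objectives. That may explain where the inputs came from. It does not justify sizing a randomised comparison on them. That the two figures are shares of one total is inferred from their sum, since the cited source is not available; the finding does not depend on it.

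A fuller protocol or analysis plan would not settle the matter either, because this article prints the comparison, test, power and N, and the comparison is the wrong one.

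**Conclusion.** The concern holds. The 80% power belongs to a boy–girl contrast in drowning, not to intervention against control on knowledge, awareness and practice. For the randomised comparison the stated power is undefined, because no control level, SD or target effect is given. What 840 per arm can detect at 80% power is about 0.20 SD if there are 42 villages per arm, 0.28 SD with 15 and 0.48 SD with 5. Those figures assume an ICC of 0.05, 10% loss, equal village sizes and no baseline adjustment, and their spread reflects the number of villages rather than the boy–girl error. N may prove adequate; the protocol's stated reason for it does not show that. The paragraph must be corrected, since it is the only support for the sample size.

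**What to change.** In Sample size calculation, delete the boy and girl inputs and the power claim attached to them. Keep N = 1680 if that is feasible. Restate power for the between-arm difference in mean six-month score, with the assumed SD, or for the difference in the proportion answering all five questions correctly, with the assumed control proportion. State the ICC and the actual number of villages per arm, reconciling the 20 and 30 parents per village and the 5 and 15 villages per arm, and report the difference detectable with 80% power.

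The cost is one rewritten paragraph and one recalculation, with no extra participants. The sponsor should expect a less favourable statement if the true village count is 15 or 5 per arm; at the calculation's own 20 parents per village it would hardly change.

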### Participants, setting and procedure

The intervention will be tested on parents with children below five years of age due to the high proportion of drowning of children aged under five years (43 % of deaths among children aged below five years in Bangladesh) [14]. Parents with children aged below five years will be collected from selected rural areas in the Rajshahi district, Bangladesh. College teachers from approximately 15 village schools will be invited to participate with other individuals from their village in a study to test the efficacy of the mobile coach based childhood drowning programme. The participating teachers will schedule one village per hour for screening the eligibility criteria, study information and baseline assessment. The study participants will be recruited by study assistants (graduate students).

The study assistants will invite all the participants from a village to participate in the survey. Furthermore, they will inform other individuals who will be invited to participate in a study to test the efficacy of mobile coach intervention for the prevention of drowning. To decrease the reporting bias, the study assistants will not provide additional information about the purpose of the study before the screening of the eligibility criteria is completed. Afterwards, the participants will be invited to complete the screening. The screening includes the assessment of demographic, environmental, behavioural data, knowledge and awareness about childhood drowning, and ownership of a mobile phone. The inclusion criteria for the study participation are (1) parents who have less than five children, children living with parents, children aged 0–4 and must have a mobile phone in the house. The exclusion criteria are (1) parents who are not available at the time of data collection (after checking the house three times) and children with a physical disability (inability to walk). Subsequently, eligible persons will be informed about the aim of the study, the intervention aims, assessments and data protection. The study information will be provided in paper form by the study assistants. After receiving informed consent, all participants will be given a username and their mobile phone number will be collected.

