### Data collection method

#### Baseline survey

Fifteen study assistants and two supervisors will collect data from the two selected union parishad (15 villages) intervention groups and two union parishad (15 villages) control groups. The study assistants will home visit and collect data from the parents through face-to-face interviews using a set of pre-tested questionnaires. The baseline survey will be conducted one month before implementation of the respective intervention packages.

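### The design effect uses 20 parents per village where the text assumes 30, and neither fits the contradictory 5 or 15 villages per arm, so the stated 80% power is not met on the plan's own inputs

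*Protocol article*

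**What the plan says.** All quotations are from the protocol article.

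- **Sample size calculation, the contrast.** The first proportion is "P1 = Proportion of drowning in boy children aged under five years 55 % = 0.55". The second is the matching share for girls, set at 0.45. The formula gives 392 per group, raised by 10% for non-response to 431, which the text says "would have 80 % power for a Chi-Square Test (*α* = 5 %, 2 *sided").
- **Sample size calculation, the clustering.** "An assumed number of participants per village of 30 and an intra-cluster correlation coefficient of 0.05 could be expected". The following sentence begins "This would result in a design effect" and inserts 20, not 30, to get 1.95. Multiplying 431 by 1.95 gives the 840 per arm and 1680 in total.
- **Randomisation and allocation concealment.** The village is the randomised unit.
- **Study settings and population.** The intervention arm is given 5 villages, and the other arm is "two union parishads (5 villages) for the control group".
- **Baseline survey.** Data come from an intervention group with 15 villages and from "two union parishad (15 villages) control groups".
- **Participants, setting and procedure.** "College teachers from approximately 15 village schools will be invited", with no split by arm.

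**The concern.** In a cluster-randomised trial the number of villages and the number of parents in each decide how much information 840 parents carry. Here the cluster size changes from 30 to 20 between one sentence and the next. Neither value fits a village count given elsewhere: 840 per arm needs 42 villages at 20 each or 28 at 30 each, while the article names 5 and 15.

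The power statement is therefore made for a design that the article does not describe. A reader cannot tell how many units will be randomised, and the shortfall may be of a kind that recruiting more parents cannot repair.

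**Working it through.** **Inputs.** Proportions 0.55 and 0.45, two-sided α 0.05, power 80%, non-response 10%, ICC 0.05, cluster size 30 (text) or 20 (formula), 840 per arm: all from Sample size calculation. Villages per arm: 5 (Study settings and population) or 15 (Baseline survey).

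**Step 1: reproduce the plan.**
- n = {1.960 × √(2 × 0.5 × 0.5) + 0.842 × √(0.55 × 0.45 + 0.45 × 0.55)}² / 0.10² = (1.386 + 0.592)² / 0.01 = 391.3, so 392.
- 392 × 1.10 = 431.2, so 431.
- Design effect (DE) = 1 + (20 − 1) × 0.05 = 1.95, and 431 × 1.95 = 840.45, so 840.

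The plan's figure reproduces, but only with 20 per village.

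**Step 2: use the assumed 30.** DE = 1 + 29 × 0.05 = 2.45, and 431 × 2.45 = 1056 per arm (2112 in total).

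**Step 3: power at 840 per arm.** Let k be villages per arm and m = 840/k. Then DE = 1 + (m − 1) × 0.05 and n_eff = 840/DE. Inverting the plan's formula, power = Φ{(0.10 × √n_eff − 1.386) / √0.495}. For 10% loss, 840 is replaced by 756 throughout, so m shrinks too.

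| Villages per arm | Basis | m | DE | n_eff | Power, all 840 | Power after 10% loss |
|---|---|---|---|---|---|---|
| 42 | implied by the inserted 20 | 20 | 1.95 | 431 | 84% | 82% |
| 28 | implied by the assumed 30 | 30 | 2.45 | 343 | 75% | 73% |
| 15 | Baseline survey | 56 | 3.75 | 224 | 56% | 55% |
| 5 | Study settings and population | 168 | 9.35 | 90 | 27% | 26% |

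The plan's 840 already includes the allowance for non-response, so the last column is the fair comparison with the stated 80%. A t reference with 2(k − 1) degrees of freedom lowers the last two rows after loss to about 53% and 22%.

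**Step 4: the ceiling.** With k fixed, n_eff = km / {1 + (m − 1) × 0.05} approaches k/0.05 as m grows. That is 100 for 5 villages (power at most 29%) and 300 for 15 (at most 69%). Both lie below the required 392. At this ICC at least 392 × 0.05 = 19.6, so 20, villages per arm are needed however many parents are recruited.

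**Step 5: sensitivity to the ICC**, after 10% loss. The values other than 0.05 are assumed.

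| ICC | 15 villages per arm | 5 villages per arm |
|---|---|---|
| 0.01 | 89% | 69% |
| 0.02 | 79% | 49% |
| 0.05 (plan) | 55% | 26% |
| 0.10 | 36% | 16% |

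**The case against.** **The ICC is only an expectation.** This stands in part. At 0.01, 15 villages per arm would be enough, and at 0.02 they give 81% with all 840 analysed and 79% after loss. But 0.05 is the plan's own value, and 5 villages fall short of 80% across the whole range shown.

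**The Baseline survey wording could mean 15 villages in each union parishad.** That would be 30 villages per arm and 28 parents per village, close to the assumed 30. The reading is possible, though less natural. DE is then 2.35 and power 76% (about 75% after loss), which is still short of 80% and still contradicts the 5 villages.

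**The remark about village schools is weak evidence.** It counts schools from which teachers are invited and gives no split by arm. It needs clarifying but does not by itself prove a contradiction. If it meant 15 villages in the whole trial (7.5 per arm, m = 112), power would be about 36%.

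**An article condenses the full protocol.** True, but nothing here is an omission: 30 and 20, and 5 and 15, are all stated figures.

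Three stronger readings are tempting, and the document does not support them:

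- A reader might infer that the trial has 26% to 55% power for its primary outcome. The 0.55 and 0.45 are boys' and girls' shares of drowning, whereas the Outcomes section scores knowledge, awareness and practice. Power for those scores cannot be computed from the article.
- A reader might multiply 431 by 3.75 and 9.35 and conclude that 1616 parents in 15 villages, or 4030 in 5, would suffice. Those products hold m at 56 and 168, so they imply about 29 (1616/56) and 24 (4030/168) villages per arm. In 15 villages, 1616 parents gives m = 108, DE 6.34, n_eff 255 and 62% power. In 5 villages, 4030 gives m = 806, DE 41.25, n_eff 98 and 29%.
- A reader might blame the whole fall on the use of 20 for 30. That slip alone takes power only to 73–75%. The rest comes from the village counts.

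**Conclusion.** The point holds as an internal contradiction with a material consequence. The cluster size in the design effect is not the one assumed, and neither agrees with a stated number of villages. On the plan's own contrast and ICC, the power of 840 per arm after 10% loss is 73% with the assumed 30 per village, 55% with 15 villages per arm and 26% with 5. In the last two cases extra parents in the same villages cannot bring it to 80%.

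The conclusion rests on an ICC of 0.05, equal village sizes and reading the Baseline survey as 15 villages per arm. It concerns the plan's stated calculation only. The contradictions in cluster size and village count stand whatever the ICC.

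**What to change.** State one number of villages per arm and use it in Study settings and population, Sample size calculation and Baseline survey. Say in Participants, setting and procedure how the approximately 15 village schools relate to it. Set m to 840 divided by that number, put that m into the design effect, and restate either the achieved power or the difference detectable with 80% power. On the plan's formula and ICC, that difference after loss is roughly 13 percentage points with 15 villages and 21 with 5, against the planned 10.

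The existing 840 and 1.95 can stay unchanged only if there are 42 villages per arm with 20 parents each. Spreading the same 1680 parents over more villages is an option only if the field plan allows it. Each arm is drawn from two union parishads, so it may mean new areas and should not be assumed cheap. At 28 villages of 30 parents it still gives only 73–75%.

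The reconciliation itself costs rewording and a less favourable stated power.

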### Intervention

The *MOBILE COACH* intervention aims to increase knowledge, safety awareness, safety behaviour and practices, and reduce the incidence of childhood drowning in Bangladesh. The SMS messages, images, videos and audio messages to reduce the incidence of drowning will be short, and in useful informal language, and, where possible, will be sent weekly (such as Friday, which is a holiday). These factors have been shown to have an impact and positively affect message acceptability when using SMSs for sexual health promotion [18]. The SMS, images, videos and audio messages will be developed by the researcher and the staff of the Centre for Injury Prevention and Research, Bangladesh. Mobile phones and the Internet are popular everywhere in Bangladesh and are well-liked by people, so we aim to determine whether they would be effective in reducing the number of children drowning.

